In France, ANSM (French National Agency for Medicines and Health Products Safety) has classified EMONO as a drug known to produce dependency. EMONO obtained its approval in 2001 in France in several indications, particularly in dental care, in hospitals exclusively, for children and patients with anxiety or disability. Its use was considered as very safe in this context [9, 10]. In 2009, the authorization to use it outside the hospital setting has led to a risk management plan implementation. The Nantes CEIP-A (Centers for the Evaluation of and Information on Drug Dependence) has been entrusted with EMONO supervision. It was shown that nitrous oxide could cause problematic consumption: 31 cases of problematic consumption of nitrous oxide alone or in a mixture with oxygen were reported over a period from 1978 to 2014 [11–37]. Classical vulnerability factors of addiction have been reported (family context, psychiatric vulnerability). Several problematic consumer groups with different characteristics have been defined: the first group includes users taking pure nitrous oxide for recreational purposes, the second group is characterized as nitrous oxide users taking it for medical purposes, and the third group is characterized as those taking it in the presence of health professionals, mainly dentists using the nitrous oxide/oxygen mixture [11–37]. However, none of the patients in the ANSM reports were described as those with dependence or abuse due to EMONO use in dental care. The desired effects in patients during EMONO use are relative anxiolysis and analgesia with a preserved state of awakening [2].

The dental service of university hospitals often represent one of the last resorts for dental care at the regional level for patients with limited cooperation because of their disabilities or anxiety. The use of EMONO is often implemented several times for each patient. Indeed, very few dentists nearby use EMONO, leading to a large influx of patients at the university hospital service. However, the authorization to use it outside the hospital setting will lead to an increasing number of dentists using EMONO.

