EMONO in paediatric dental care is particularly useful in which EMONO can be administered as the first psychoactive substance known for its positive effects (euphoria). Health professionals observe children who take EMONO daily. The main objective of this project is to evaluate the effects sought and felt by children when EMONO is used in paediatric dentistry. The secondary objectives are to (i) evaluate the appreciation of EMONO by a child, (ii) characterize children who experience both analgesia and anxiolysis, (iii) evaluate children’s appetite for EMONO and characterize children with high appetite and (iv) evaluate the impact of various product applications among the French dental service university hospitals on anxiety. The maintenance of the framework for the safe use of this drug, which is placed in dental care as fundamental, and the benefit ratio as very favourable, is essential. Twelve French dental service university hospitals have agreed to set up this study.

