## Methods

### Study design

This observational, descriptive, transversal study aims to evaluate the effects sought and felt by children when EMONO is used in paediatric dentistry. Subjects needing dental care under EMONO were recruited by 12 French dental service university hospitals. Thereafter, the data are collected by practitioner observation, direct interview after dental care under EMONO and using the subject’s medical record.

This project received the financial support from the French National Agency for Medicines and Health Products Safety (ANSM) as part of the 2017 ‘national call for tender’ and also received funding from the local Scientific Committee of the Faculty of Dental Surgery in Nantes as part of the 2017 call for tender.

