#### Primary endpoint

Our primary endpoint, to describe the effects of EMONO that are felt and sought during care during the first and last treatment sessions, will be performed by questioning the patients comprehensively about the presence or absence of each expected effect of EMONO (waking state preserved, no abolition of judgment, relative analgesia, anxiolysis), and each adverse event (slight decrease in consciousness, agitation, anxiety, euphoric effect, nausea or vomiting, sensation distortion) at the first and last treatment sessions. The presence of unexpected “other” effects will also be indicated. When scored as present, all effects will be considered as experienced by the patient.

For each effect felt, the patient will be asked about his or her perception of the effect (positive or not).

To describe the effects felt and sought with EMONO use, the prevalence of each effect felt will be calculated, and the proportion of patients who felt this effect and found it pleasant (positive) will also be indicated.

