#### Secondary endpoints

*Three parameters will be used to evaluate the child’s assessment of EMONO during the first session of care:*
VAS (Visual analogue scale): the patient marks on the line the point he/she feel represents their perception and eventually their appreciation of contact with EMONOChoice of the child with an adapted drug-liking test: the patient will be asked if he/she prefers to exchange the toy that he/she traditionally receives at the end of the care against an EMONO inhalation without care [38, 39]The child’s will to continue care in the case of adverse effects

*Three parameters will define children who experience both analgesia and anxiolysis during the first session of care:*
Decreased score on the anxiety scale (Venham modified by Veerkamp) before and after inhalation of EMONOPresence of anxiolysis among the effects feltPresence of analgesia among the effects felt

We will estimate the prevalence of children for whom at least one of the first two parameters and the third parameter are present during the same session of EMONO use.

*The parameter “Presence of signs that the child is trying to prolong contact with EMONO” will be used to define patients with a higher appetite for EMONO (shown by patients’ attempt to extend the duration of EMONO use physically or verbally) during the first session of care. The following three parameters will characterize these children:*
Table answering the questions about the presence of expected effects of EMONO and their perceptionsMedical historyFamily situation of parents and anxiety of parents [40–42]

*Three parameters will make it possible to evaluate the impact of the difference of practice between the French dental service university hospitals regarding the anxiety during the first and last sessions of care:*
Decreased score on the anxiety scale (Venham modified by Veerkamp) before and after inhalation of EMONOUse of a sedative premedicationPatient management using closed boxes or open spaces

The different practices evaluated in the French dental service university hospital will include the use or absence of a sedative premedication and management of the patient in closed or open boxes.

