### Statistical methods

All the evaluation parameters will be subjected to a descriptive analysis. The quantitative variable evaluation parameters will be described using position parameters (mean or median) and dispersion (standard deviation, interquartile range and range). Normality of their distribution will be assessed (normality test and evaluation using the relevant graphic tools). The qualitative variable evaluation parameters will be shown in the form of number and frequency tables for each modality.

To answer the main objective (description of the effects felt and sought using EMONO), the prevalence of each effect felt will be calculated, and the proportion of patients who felt this effect and found it pleasant (positive) will also be indicated.

Each criterion to evaluate the EMONO’s assessment by the child will be analysed independently (average for the VAS score, prevalence of drug-liking and continuation of care).

The prevalence of children who experience both analgesia and anxiolysis will be estimated. A multivariate logistic regression model will be applied to define the associated factors: child/parent socio-demographic characteristics and antecedents.

The prevalence of children with a higher appetite for EMONO will be estimated. A multivariate logistic regression model will be applied to define the associated factors: socio-demographic child/parent characteristics, medical history, presence of expected EMONO effects and their perceptions.

The impact of care practices (sedative premedication and closed/open box management) on anxiety will be evaluated using average comparisons (Student’s tests) of the anxiety score before and after the inhalation of EMONO. A comparison will also be made on the difference in the pre- and post-inhalation score.

The evolution of EMONO intake between the first and last sessions will be described in terms of the prevalence (amnesic effect, tolerance, concern), appetite difference and difference between the effective dosage at the first and last treatment sessions will be calculated.

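### The single model for higher appetite adjusts factors present before inhalation for effects and perceptions that arise from it, which may attenuate the former; a model with pre-inhalation factors alone should be stated alongside it

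*Protocol article*

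**What the plan says.** Objective (iii) is to "evaluate children’s appetite for EMONO and characterize children with high appetite" (Background). Under Secondary endpoints, higher appetite is a sign, during the first session, that the child wants longer contact with the gas, "shown by patients’ attempt to extend the duration of EMONO use physically or verbally". The same section names three sets of characterizing parameters: the table of expected effects and their perceptions, medical history, and family situation with parental anxiety.

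Statistical methods turns this into one analysis: "A multivariate logistic regression model will be applied to define the associated factors", with the factors given as "socio-demographic child/parent characteristics, medical history, presence of expected EMONO effects and their perceptions". No order of entry or second model is mentioned. The model for children with both analgesia and anxiolysis, in the same section, lists only "child/parent socio-demographic characteristics and antecedents".

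On timing, Study design lists "direct interview after dental care under EMONO" among the data sources, and Primary endpoint says: "For each effect felt, the patient will be asked about his or her perception of the effect (positive or not". The Background notes, for nitrous oxide in general: "Classical vulnerability factors of addiction have been reported (family context, psychiatric vulnerability".

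**The concern.** The list mixes two kinds of variable. Socio-demographic characteristics and medical history are fixed before the mask goes on. Effects and their perceptions exist only because the child inhaled, and they are reported after the session in which the attempt to prolong was or was not seen. Entered together, the background factors get odds ratios that are conditional on that experience.

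Suppose a background factor makes a child more likely to feel an expected effect or to find it positive, and this makes the child more likely to try to prolong inhalation. The experience variables then absorb part or all of the factor's association. The model would answer whether the factor matters among children with the same reported experience. A reader who wants to know which children are more likely to show higher appetite needs the association without that conditioning, and the stated plan has no model that gives it.

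**Working it through.** **The plan's own figure.** The Discussion says that characterizing children with higher appetite needs 1291 patients at an alpha risk of 5%, based on the pilot (12 of 76, stated as 16%). A precision formula with an assumed half-width of 2 points reproduces it:

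n = 1.96² × 0.16 × 0.84 / 0.02² = 3.8416 × 0.1344 / 0.0004 = 1291.

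The half-width is inferred from the match, and some two-group calculations with other unstated inputs come within 3%. The figure therefore does not show that the regression was sized. With 1300 patients, 1300 × 12/76 ≈ 205 children with higher appetite are expected.

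**Inputs for the illustration.** From the document: the recruitment aim of 1300 and the pilot appetite rate of about 16%. Assumed: a background factor present in 20% of children, one binary variable for a positively perceived effect, and all strengths of association. Each scenario uses 600 simulated data sets with a two-sided 5% test.

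**First set: full mediation, fixed probabilities.** Appetite rate in a group = P(effect) × rate with effect + (1 − P(effect)) × rate without.

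- Scenario (a): effect in 70% with the factor and 40% without; appetite 32% with the effect and 5% without it. With the factor: 0.70 × 0.32 + 0.30 × 0.05 = 0.239. Without: 0.40 × 0.32 + 0.60 × 0.05 = 0.158. Total OR = (0.239/0.761) / (0.158/0.842) = 1.67.
- Scenario (b): effect in 65% and 40%; appetite 26% and 8%. With the factor: 0.65 × 0.26 + 0.35 × 0.08 = 0.197. Without: 0.40 × 0.26 + 0.60 × 0.08 = 0.152. Total OR = (0.197/0.803) / (0.152/0.848) = 1.37.

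**Second set: odds-ratio inputs.** The effect occurs in 30% of children without the factor, and overall appetite is calibrated to 12/76.

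| Scenario | OR, background factors only | OR, effect added | Power, background factors only | Power, effect added |
|---|---|---|---|---|
| (a) full mediation | 1.67 | 1.00 | 84% | 5% |
| (b) full mediation | 1.37 | 0.99 | 41% | 5% |
| Full; factor→effect OR 3, effect→appetite OR 5 | 1.48 | 0.98 | 60% | 4% |
| Full; OR 3 and OR 3 | 1.33 | 0.99 | 32% | 4% |
| Full; OR 2 and OR 3 | 1.20 | 1.00 | 18% | 6% |
| Partial; OR 3 and OR 5, plus direct OR 1.5 | 2.15 | 1.48 | about 100% | 61% |
| None; direct OR 2, effect→appetite OR 3 | 1.92 | 1.97 | 94% | 95% |

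By construction the odds ratio with the effect added is 1 under full mediation, 1.5 in the partial scenario and 2 in the last row. Small departures are simulation noise. The slight rise in the last row reflects that odds ratios change somewhat when any predictor of the outcome is added.

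**The case against.** **The aim is descriptive.** The study calls itself observational and descriptive, the model seeks associated factors, and Secondary endpoints names effects and perceptions first among the characterizing parameters. This stands: including them is not an error. The Background sentence on vulnerability factors comes from reports of problematic nitrous oxide use, and finding such factors is not a stated objective. The contrast with the analgesia and anxiolysis model also proves little, since there the effects are the outcome.

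**The likeliest mediators are mostly outside the list.** The model holds expected effects, which Primary endpoint defines as preserved wakefulness and judgment, analgesia and anxiolysis. Euphoria is listed there as an adverse event, and the VAS and the drug-liking test are analysed separately. A reader might infer that the model compares children who liked the gas equally, or that pleasantness will dominate it. The stated list supports neither.

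**The pilot found nothing.** No collected variable was significantly associated with prolongation. Scenario (a) implies an effect-to-appetite OR of (0.32/0.68) / (0.05/0.95) = 8.9, which 76 children would detect about 86% of the time (Fisher test). Scenario (b) implies 4.0, detected about half the time. The article does not say whether perceptions were among the pilot variables, so this is not decisive, but scenario (a) should be read as an upper end.

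**Staging belongs in the SAP.** In part. Order of entry can be left there, and nothing excludes nested models. But the article does state a covariate list, and the point concerns what that list yields. If the SAP already reports a model with pre-inhalation factors only, the point is met.

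**Conclusion.** The point holds as a modest, inexpensive improvement to a secondary analysis. As written, the odds ratios for socio-demographic characteristics and medical history are conditional on what the child felt and found positive, and no stated model gives them without that condition. Any loss depends on how far background factors act through the expected effects and their perception: down to about 1 if entirely (from 1.2–1.7), from 2.15 to about 1.5 in the partial scenario, and none if not at all. The factor prevalence, the single binary mediator and the strengths are assumptions; only the time order comes from the document.

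A reader might go further and infer that the model will erase the vulnerability factors, or that a null result will be taken to mean no vulnerable group exists. The documents support neither: mediation is not shown, and nothing says how a null would be interpreted. The primary descriptive prevalences, the prevalence of higher appetite and the figure of 1291 are unaffected.

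**What to change.** In Statistical methods, replace the single model for higher appetite with two nested models.

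- **Model 1** contains only factors present before inhalation: socio-demographic and family characteristics, and medical history. It is used to describe which children are more likely to show higher appetite.
- **Model 2** adds the expected effects and their perceptions, reported as the experience that accompanies appetite. State that the odds ratios of pre-inhalation factors in this model are not to be read as evidence that those factors do not matter.

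All the data are already to be collected. The cost is one extra table and two sets of odds ratios to explain.

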### Study size

The evaluation of the effects sought and felt by children when EMONO is used in paediatric dentistry does not require any sample size calculation. The dental service of Nantes University Hospital manages between 8 and 10 patients eligible for research per week and has a national average of numbers supported by participating dental services.

This estimate allows a 12-month inclusion potential, which represents between 5000 and 6000 patients. Considering a ratio of one eligible patient out of three to four to include, the recruitment aim is 1300 patients. The period of inclusion was set at 12 months to ensure that the study would be proposed to a maximum of eligible patients.

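### Objective (iv) compares practices that differ between 12 hospitals with unadjusted Student tests that ignore hospital, so the result cannot be attributed to the practice, and error is inflated where practice clusters by hospital

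*Protocol article*

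**What the plan says.** The Secondary endpoints section sets the question as to "evaluate the impact of the difference of practice between the French dental service university hospitals regarding the anxiety", at the first and last sessions. The practices compared are "the use or absence of a sedative premedication and management of the patient in closed or open boxes", and the outcome is the fall in the modified Venham anxiety score around inhalation.

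The Statistical methods section fixes the analysis: "The impact of care practices (sedative premedication and closed/open box management) on anxiety will be evaluated using average comparisons", namely Student tests on the score before and after inhalation. I read this as a comparison of practice groups at each time point. It then adds: "A comparison will also be made on the difference in the pre- and post-inhalation score". No hospital term, clustered variance or covariate is named. The same section does name multivariable logistic models for two other objectives: children with both analgesia and anxiolysis, and children with higher appetite.

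The study is observational. On its size, Study design says "Subjects needing dental care under EMONO were recruited by 12 French dental service university hospitals" and Study size says "the recruitment aim is 1300 patients".

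**The concern.** A Student test assumes independent observations and attributes the whole difference in means to the grouping variable. Neither suits this question.

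- **Independence.** Children at one hospital share case mix, staff and raters, since the dentist completes the survey partly from personal observation. If practice also tends to go with hospital, the pooled standard error is too small.
- **Attribution.** Practice is not randomised. Where it goes with hospital, a crude contrast of open and closed boxes is also a contrast of everything else that differs between those hospitals.
- **Possible confounding by indication.** Where premedication varies between children within a hospital, it may go to children whose anxiety differs from the rest.

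At stake is a national report in which a difference between hospitals is presented as the impact of premedication or room type.

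**Working it through.** **Inputs from the protocol article.** There are 12 hospitals and an aim of 1300 children. The article gives no power or precision figure for this comparison. Its figure of 1291 concerns appetite only. The recruitment aim is consistent with its own basis: 8 to 10 eligible per week × 52 × 12 = 4992 to 6240 (stated as 5000 to 6000), and one in three to four of 5000 to 6000 is 1250 to 2000, which contains 1300.

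**Assumptions, not in the article.** Two-sided 5% level for these tests (5% is stated only for the appetite calculation); equal hospital sizes; a range of ICCs for the anxiety score; no true effect of practice.

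**Step 1. Practice set wholly by hospital.** Children per hospital m = 1300/12 = 108.3. Design effect DE = 1 + (m − 1) × ICC. Effective sample size = 1300/DE. True error of a nominal 5% test = 2 × [1 − Φ(1.96/√DE)].

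At ICC 0.01: DE = 1 + 107.3 × 0.01 = 2.07; √DE = 1.44; 1.96/1.44 = 1.36; error = 17.3%.

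| ICC (assumed) | DE | Effective N | Error by formula | Simulated, 6 v 6 hospitals |
|---|---|---|---|---|
| 0.005 | 1.54 | 846 | 11.4% | 11.3% |
| 0.01 | 2.07 | 627 | 17.3% | 17.3% |
| 0.02 | 3.15 | 413 | 26.9% | 26.8% |
| 0.05 | 6.37 | 204 | 43.7% | 43.9% |
| 0.10 | 11.73 | 111 | 56.7% | 56.6% |

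The simulation used 12 hospitals × 108 children and 20,000 runs per setting. Splits of 3 v 9 and 2 v 10 hospitals gave the same picture.

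**Step 2. Practice varying within hospitals.** Same layout, 30% overall use, 3,000 runs per setting. The between-hospital correlation of practice measures how strongly its use clusters by hospital.

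| Correlation of practice | ICC 0.01 | ICC 0.05 | ICC 0.10 |
|---|---|---|---|
| 0 (equally common everywhere) | 5.3% | 5.1% | 5.6% |
| 0.1 | 5.6% | 10.9% | 17.4% |
| 0.3 | 8.0% | 21.7% | 31.2% |
| 0.6 | 11.7% | 32.4% | 46.6% |

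Inflation needs both a non-zero ICC and practice that clusters by hospital.

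**Step 3. Does accounting for hospital repair the error rate?** With practice set by hospital, a t test on the 12 hospital means gave 4.7% to 5.3% in all settings with non-zero ICC. With practice varying within hospitals, a model with hospital effects gave 4.6% to 6.1%. These figures concern error rate only; they say nothing about confounding.

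**The case against.** **The full analysis plan may add a hospital term.** That would be a fair answer to silence, but the article is not silent. It names the test for this objective and names adjusted models for two others.

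**The error rate is not known to be high.** This stands. The article gives no ICC, no level for these tests and no statement that either practice is uniform within a hospital. Both practices could be recorded child by child. A reader might infer that false positives will far exceed 5%; the document does not support that as a fact, because the error stays near 5% if a practice is equally common everywhere. That favourable case, however, would leave nothing to learn about differences in practice between hospitals, which is the stated objective.

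**The two mechanisms do not apply in full to the same practice.** This also stands. The largest figures need practice fixed by hospital, whereas confounding by indication needs it to vary between children within a hospital. A reader might infer that premedication goes to the more anxious child. That is plausible, but the article does not say how premedication is chosen.

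**The change score deals with baseline differences.** It removes part of a baseline difference. It does not remove hospital effects on the change, or regression to the mean.

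**Multiplicity.** A reader might count two practices, two sessions and three scores as 12 independent tests and compute a familywise error. Independence cannot hold: the change score is an exact function of the other two scores, and the two sessions share children. No such figure is used here.

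**The objective is secondary in a descriptive study.** This is true and bears on severity. The primary prevalences do not depend on this analysis.

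**Conclusion.** The concern holds in conditional form. The article fixes a crude child-level test for a question it defines as a difference between hospitals. That test cannot separate a practice from other hospital differences, and this follows from the design without any assumed figure.

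The effect on error rate depends on quantities the article does not give. At an assumed 5% level it runs from about 5% (practice equally common everywhere), through 8% to 31% (correlation of practice 0.3, ICC 0.01 to 0.10), to 11% to 57% (practice set wholly by hospital, ICC 0.005 to 0.10). Confounding by indication for premedication is possible, not documented.

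This should be fixed before analysis. It is not critical to the study, because the objective is secondary and the primary endpoint is unaffected.

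**What to change.** Replace the Student tests for objective (iv) as follows.

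- Use a mixed model for the anxiety score that accounts for hospital, with small-sample degrees of freedom reflecting 12 hospitals. For a practice that proves uniform within hospitals, use a centre-level analysis.
- Enter both practices together, and adjust for age, medical history and parental anxiety.
- State how pre-inhalation anxiety is handled. It is the natural baseline, but it may already reflect premedication, so adjusting for it could remove part of what is being studied.
- Where a practice varies within hospitals, report the within-hospital contrast. A random intercept alone does not remove hospital-level confounding.
- Report differences with 95% confidence intervals, worded as associations and not as impact.

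The cost is revised analysis wording, slightly more analysis and wider confidence intervals. Hospital is known for every child, so accounting for it needs no new data.

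### If the pre-inhalation anxiety score follows premedication, the planned pre/post difference does not measure premedication's effect; the article fixes neither that timing nor the deciding comparison

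*Protocol article*

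**What the plan says.** The fourth secondary objective asks how differing practices between the participating hospitals affect children's anxiety. Under Secondary endpoints, the practices are "the use or absence of a sedative premedication and management of the patient in closed or open boxes". The only anxiety parameter listed there for this objective is the decrease in the modified Venham score from before to after EMONO inhalation, at the first and last sessions.

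Statistical methods then gives two analyses. The impact of the practices "will be evaluated using average comparisons (Student’s tests) of the anxiety score before and after the inhalation of EMONO". The next sentence adds: "A comparison will also be made on the difference in the pre- and post-inhalation score".

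The same section plans multivariate logistic models for two other objectives (combined analgesia and anxiolysis; higher appetite). It names no covariates for this one.

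No section says when the pre-inhalation score is taken relative to premedication, and no anxiety score before premedication is described. The design is non-randomised: "This observational, descriptive, transversal study aims to evaluate the effects sought and felt by children when EMONO is used in paediatric dentistry".

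**The concern.** A premedication is given ahead of the procedure it prepares for. A score described only by its position before inhalation is therefore most naturally read as taken once premedication has been given. On that reading the exposure has already acted on the starting value. The pre/post difference then answers a different question: how much further anxiety falls under EMONO in children who did or did not receive premedication. A premedication that works lowers the starting score and leaves less to fall.

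At stake is the conclusion on a stated objective. A useful premedication could appear neutral or unhelpful on the one anxiety parameter that Secondary endpoints names. If the separate score comparisons pointed the other way, nothing in the plan says which should be believed.

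**Working it through.** **Inputs.** The outcome and exposures come from Secondary endpoints, the tests from Statistical methods and the lack of randomisation from Study design. The article gives no scale range, mean, SD, effect size or power for this comparison, so there is no plan figure to reproduce. All numbers below are assumptions chosen to show direction.

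**Step 1: algebra, with the pre-inhalation score taken after premedication.** Let m be mean anxiety before any premedication, d the lowering by premedication before inhalation, r the share of d remaining after inhalation, and e the fall due to EMONO.

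| | Pre | Post | Fall |
|---|---|---|---|
| No premedication | m | m - e | e |
| Premedication | m - d | m - e - rd | e - (1-r)d |
| Contrast | -d | -rd | -(1-r)d |

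A negative contrast in a score favours premedication. A negative contrast in the fall counts against it.

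**Step 2: values put in.**

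| d | r | Pre contrast | Post contrast | Contrast in fall |
|---|---|---|---|---|
| 1.0 | 1.0 | -1.0 | -1.0 | 0.0 |
| 1.0 | 0.5 | -1.0 | -0.5 | -0.5 |
| 1.0 | 0.0 | -1.0 | 0.0 | -1.0 |
| 0.5 | 1.0 | -0.5 | -0.5 | 0.0 |
| 0.5 | 0.5 | -0.5 | -0.25 | -0.25 |
| 0.5 | 0.0 | -0.5 | 0.0 | -0.5 |

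The contrast in falls never credits premedication. A fully persisting benefit disappears, and a waning one is shown as a disadvantage.

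**Step 3: EMONO acting proportionally.** Two identical children start at 3. One is brought to 2 by premedication, and EMONO then halves both scores. Post scores are 1.5 without and 2/2 = 1.0 with premedication, a benefit of 0.5. Falls are 3 - 1.5 = 1.5 and 2 - 1.0 = 1.0, so premedication looks worse by 0.5. No confounding is involved.

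**Step 4: floor.** A simulation used an assumed 0 to 5 score, rounded to whole points, with latent mean 2.5, latent SD 1.3, measurement SD 0.5, d = 1.0 and the same latent EMONO effect in both groups.

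| e | Fall without | Fall with | Contrast in fall | Post contrast |
|---|---|---|---|---|
| 1.0 | 0.91 | 0.76 | -0.15 | -0.76 |
| 2.0 | 1.67 | 1.26 | -0.41 | -0.50 |

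**Step 5: the other timing.** If the pre-inhalation score is taken before premedication, both groups start at m. The falls are e and e + rd, and the contrast is +rd, for example +0.5 for d = 1.0 and r = 0.5. The difference then includes the premedication effect with the right sign, and the problem does not arise.

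**The case against.** **The timing is inferred.** Premedication precedes EMONO, but that does not prove the child was rated after it. Rating times are also a detail that an article may leave to the full protocol. This stands, and the point is conditional for that reason. The article itself, however, fixes the parameter and the comparison, and the meaning of both depends on that timing.

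**The plan does not rest on the difference alone.** Statistical methods first plans Student's tests on the pre- and post-inhalation scores, and the difference is an addition. If those tests compare practices at each time, the example in step 3 would give 3 v 2 and 1.5 v 1.0, both favouring premedication. This also largely stands. A reader might infer that the study would report premedication as having no impact or a harmful one; the documents do not support that, because these companion tests may show the effect. Their wording also allows a paired before-versus-after reading, which would not compare practices at all.

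**The pre-inhalation comparison is not itself a mistake.** A reader might object that it uses a value measured after exposure. An outcome should be measured after exposure, and on the assumed timing this test shows the premedication effect before EMONO acts.

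**Reversal is not inevitable.** With an equal additive fall of 1 (3 to 2 and 2 to 1) and a persisting effect, nothing reverses. That is correct, but the falls are then equal and a 1-point benefit is invisible in the difference.

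**The post-inhalation score has its own bias.** If more anxious children are premedicated (an assumption), take one going 4.5 to 3.5 with premedication and then to 1.75, against another going 3 to 1.5. Premedication looks worse by 0.25 after inhalation although it lowered anxiety by 1 point beforehand. This stands and limits what any remedy without an earlier rating can claim.

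**Conclusion.** The point holds conditionally. If the pre-inhalation score follows premedication, which is the natural reading but is not stated, the pre/post difference estimates change under EMONO by premedication status. It removes a persisting premedication effect. It can take the wrong sign when that effect wanes, when EMONO acts proportionally, or when scores reach the floor. The bias in the contrast of falls follows from the algebra; its size in this study cannot be known, because the article gives no scale range, spread or effect.

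Independently of timing, the comparisons are planned as unadjusted tests in a non-randomised study, and no rule says which of them answers the objective. This concerns one secondary objective and leaves the primary description of effects untouched. It matters because it decides what can be concluded about premedication. The same question of timing arises for closed or open boxes if the child is already in that setting when first rated.

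**What to change.** 1. State when the pre-inhalation score is taken relative to premedication, and whether this is the same in all 12 centres.
2. If it follows premedication, do not read the pre/post difference as the impact of premedication. Report it as *change under EMONO by premedication status*.
3. Make between-group comparisons of the pre-inhalation and post-inhalation scores the analysis for premedication, and say in advance that these answer the objective. Replace the unadjusted Student's tests with a regression adjusted for collected variables fixed before premedication, such as age, medical history, parental anxiety and centre. Under this timing, do not adjust the post-inhalation score for the pre-inhalation score, because that would remove part of the effect being estimated.
4. Report the result as an association. Without an anxiety rating before premedication, confounding by indication remains.

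The cost is a few sentences in the analysis plan and one regression per score and session on data already collected. One limit should be stated: with centre as a fixed effect, centres that premedicate every child or none add no information to the contrast, and the article does not say how far use varies within centres. Patient care is not affected.
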